## Abstract

**Background:**

Costs of in vitro fertilisation (IVF) are high, which is partly due to the use of follicle stimulating hormone (FSH). FSH is usually administered in a standard dose. However, due to differences in ovarian reserve between women, ovarian response also differs with potential negative consequences on pregnancy rates. A Markov decision-analytic model showed that FSH dose individualisation according to ovarian reserve is likely to be cost-effective in women who are eligible for IVF. However, this has never been confirmed in a large randomised controlled trial (RCT). The aim of the present study is to assess whether an individualised FSH dose regime based on an ovarian reserve test (ORT) is more cost-effective than a standard dose regime.

**Methods/Design:**

Multicentre RCT in subfertile women indicated for a first IVF or intracytoplasmic sperm injection cycle, who are aged < 44 years, have a regular menstrual cycle and no major abnormalities at transvaginal sonography. Women with polycystic ovary syndrome, endocrine or metabolic abnormalities and women undergoing IVF with oocyte donation, will not be included. Ovarian reserve will be assessed by measuring the antral follicle count. Women with a predicted poor response or hyperresponse will be randomised for a standard versus an individualised FSH regime (150 IU/day, 225-450 IU/day and 100 IU/day, respectively). Participants will undergo a maximum of three stimulation cycles during maximally 18 months. The primary study outcome is the cumulative ongoing pregnancy rate resulting in live birth achieved within 18 months after randomisation. Secondary outcomes are parameters for ovarian response, multiple pregnancies, number of cycles needed per live birth, total IU of FSH per stimulation cycle, and costs. All data will be analysed according to the intention-to-treat principle. Cost-effectiveness analysis will be performed to assess whether the health and associated economic benefits of individualised treatment of subfertile women outweigh the additional costs of an ORT.

**Discussion:**

The results of this study will be integrated into a decision model that compares cost-effectiveness of the three dose-adjustment strategies to a standard dose strategy. The study outcomes will provide scientific foundation for national and international guidelines.

**Trial registration:**

NTR2657

## Background

In vitro fertilisation (IVF) is the treatment of last resort for many subfertile couples and a very costly one, partly due to the use of expensive drugs, i.e. gonadotrophins, needed for controlled ovarian hyperstimulation (COH) [1]. COH is an essential part of IVF which is needed to obtain a reasonable yield of oocytes which can then be fertilised in vitro. In clinical practice physicians often rely on their clinical experience and judgement when selecting an appropriate starting dose of follicle stimulation hormone (FSH). There is neither international nor nationwide consensus about COH programmes. Defining the optimal dose of FSH to retrieve an acceptable number of oocytes remains complicated. The problem herewith is that women show marked differences in their ovarian reserve and, as a consequence, in their ovarian response to medication [2,3]. Women who respond poorly to ovarian stimulation have poorer pregnancy prospects than women with a normal ovarian response [4]. Frequently, the occurrence of an insufficient response will urge the clinician to cancel the cycle which is obviously very stressful to the couple and may lead to withdrawal from further treatment. In a subsequent stimulation cycle higher dosages of FSH are usually given, although these may also be inadequate, leading to another cancellation of the cycle or even to hyperresponse with risk of ovarian hyperstimulation syndrome (OHSS). The result is that the poor responder may go through a series of treatment cycles with an overall poor prospect for pregnancy.

On the other end of the spectrum, women with a hyperresponse to ovarian stimulation are at risk of increased patient discomfort, cycle cancellation and development of OHSS. This condition may lead to severe illness requiring hospitalisation and intensive care with thromboembolic phenomena or multiple organ failure which are potentially life threatening complications. Mild and moderate forms of OHSS occur in respectively 20–33% and 3–6% of all ovarian stimulation cycles, while the severe form of the syndrome has been reported to occur as frequently as 0.1–2% [5].

In view of the tight relationship between hyperresponse and OHSS, prevention of hyperresponse is one of the key elements in preventing OHSS. Accurate prediction of ovarian response is now possible by using an ovarian reserve test (ORT) [6]. Various ORTs are available, of which basal FSH is the oldest whereas the antral follicle count (AFC) and serum level of anti-Müllerian hormone (AMH) have been introduced more recently. Previous systematic reviews by our group have shown that both AFC and AMH provide an optimal balance between sensitivity and specificity, are superior to basal FSH, and are able to predict ovarian response to COH, allowing for studies on the value of adjustment of the FSH dosage based on these parameters [6-10]. It should be emphasised that our reviews showed that ORTs can predict ovarian response after COH, but not the occurrence of pregnancy after IVF treatment.

Previous research has shown that dose adjustment after ORTs resulted in a higher rate of normal ovarian response and significantly higher pregnancy rates [11]. However, this study had several weaknesses. First of all, the power calculation was not based on the outcome ‘pregnancy’ but on the outcome ‘appropriate response’. Furthermore, participants with possible extremes in ovarian response were excluded, FSH dosage was only fixed until stimulation day 8, and the used algorithm was complicated and impractical for daily clinical use. Before definitive conclusions can be drawn about dose adjustment after ORTs, these results need to be confirmed in a large randomised controlled trial (RCT). Based upon these data, we hypothesize that the use of an ORT as predictor of ovarian response followed by an individualised FSH regime, will lead to a reduction in the occurrence of an inappropriate ovarian response, a reduction in the amount of cycle cancellations, reduction in the number of withdrawals from treatment, reduction in the occurrence of OHSS, reduction in the application of cycles with poor prospects for success, improvement in overall pregnancy rates and improvement of overall cost-effectiveness of IVF programs.

## Methods

### Study design

The OPTIMIST trial is a nationwide multicentre RCT. The cohort will consist of 1,500 women screened for ovarian reserve by an AFC prior to IVF or intracytoplasmic sperm injection (ICSI) treatment. Two RCTs are embedded in this cohort. Based on the AFC, women will be classified into four categories; AFC less than 8 (predicted poor responders), AFC 8-10 (predicted low-normal responders), AFC 11-15 (predicted normal responders) or AFC above 15 (predicted hyperresponders). RCT 1 will contain 300 women with an AFC below 11; RCT 2 will contain 300 women with an AFC of more than 15. A total of 25 academic and non-academic centres in the Netherlands will participate. An economic analysis is incorporated to assess the cost-effectiveness of an ORT and subsequent individualised FSH dosage in IVF or ICSI treatment. Inclusion was started in May 2011. This study will be conducted in accordance with the principles of the Declaration of Helsinki and in accordance with Good Clinical Practice. The study protocol has been approved by the Institutional Review Board (IRB) of the University Medical Center Utrecht (MEC 10-273) and by the board of directors of all participating centres.

### Sample size calculation

Based on the expected gain in pregnancy rate resulting in live birth as reported in the study by Popovic-Todorovic et al. [12], we expect an increase in pregnancy rate over three IVF or ICSI cycles of 15% (from 25% to 40%) in the predicted poor responders (RCT 1). To demonstrate that such a difference will occur, we need to include 300 couples in RCT 1 (alpha-error of 0.05 and a power of 80%, two-sided test). If we expect a positive effect of dose adjustment in both the predicted poor responders (RCT 1) and predicted hyperresponders (RCT 2), the total sample size of 600 women, in both RCTs, allows the detection of an increase in pregnancy rate from 30% after conventional treatment to 41% in the dose adjustment group (alpha-error of 0.05 and a power of 80%, two-sided test). If the net effect of dose adjustment on pregnancy rate is less than 11%, it is unlikely that an ORT and dose adjustment is cost-effective. The assumed 30% success rate in the conventional group in the latter calculation is higher than the assumed 25% success rate in the conventional group of solely RCT 1, as RCT 1 only contains women with an expected poor response. RCT 2 adds women with a predicted hyperresponse, who are expected to have higher pregnancy rates. For RCT 2 an increase in pregnancy rate from 35% to 42% over three cycles is expected. With 300 participants the power to detect this difference is 24%.

In our Individual Patient Data meta-analysis on 2,300 patients in 13 studies, we found that 25% had and AFC below 6, 18% had an AFC between 6 and 9, 33% had an AFC between 10 and 15 and 24% had an AFC of more than 15 [12].If we assume that 20% of the couples will have a low or low-normal ovarian reserve, and are therefore eligible for the predicted poor responder trial, we need to include a cohort of 1,500 women for ovarian reserve screening in order to achieve the necessary number of participants for the two trials. This will then allow a sample size of just over 300 women for RCT 1.

A sample size calculation for the cost effectiveness analysis is not provided. It is generally accepted that this type of sample size is not provided because the uncertainty of the cost economy ratio is largely determined by the variation in the efficacy (the denominator of the ratio) and can therefore not be performed at a realistic level.

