### Economic analysis

From a societal perspective, we will perform an economic analysis alongside the cohort study and clinical trials. The data on cancellation rates, FSH consumption and pregnancy rate from the cohort study (900 couples) and the two RCTs (300 patients per study) will be integrated in a cost-effectiveness analysis. We will build on previous work that we have done for CVZ (College Voor Zorgverzekeringen; College of Health Insurances). In the analysis, we will assess the cost-effectiveness of using an ORT for dose adjustments in poor responders ór hyperresponders only and using an ORT for dose adjustment in both poor responders and hyperresponders, as compared to current practice where no ORT is used and standard FSH doses are given.

The study design will enable us to compare the costs and effects of the following strategies:

I. IVF or ICSI without an ORT for three cycles with a standard start dose (reference strategy)

II. ORT followed by IVF or ICSI with dose adjustment in women with predicted hyperresponse and predicted poor response

III. ORT followed by IVF or ICSI and dose reduction in women with predicted hyperresponse only

IV. ORT followed by IVF or ICSI and dose adjustment in women with predicted poor response only

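### The 1,500-woman cohort assumes 20% eligible for RCT 1, but the plan's own data give at least 43%, so the 900/300/300 composition does not follow

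*Protocol article*

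**What the plan says.** Under Study design, a cohort of 1,500 women is screened by AFC and two trials are embedded in it: "RCT 1 will contain 300 women with an AFC below 11" and "RCT 2 will contain 300 women with an AFC of more than 15". AFC 11-15 defines the predicted normal responders.

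Under Sample size calculation, the authors cite their own meta-analysis of 2,300 patients. At the low end it found that "25% had and AFC below 6, 18% had an AFC between 6 and 9". For the remaining women the figures are 33% at AFC 10-15 and 24% above 15. The next sentence reads "If we assume that 20% of the couples will have a low or low-normal ovarian reserve". It treats this share as the women who qualify for RCT 1 and concludes that 1,500 women must be screened, giving just over 300 for RCT 1. No reason is given for moving from the reported distribution to 20%.

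Under Recruitment, consent and randomisation, all participants other than the predicted normal responders are randomised. No closing rule for either trial is stated.

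Under Economic analysis, the data sources are "the cohort study (900 couples) and the two RCTs (300 patients per study").

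**The concern.** Two adjacent sentences disagree. RCT 1 includes both of the lower AFC bands in the cited data, and AFC 10 as well. The band below 6 alone, at 25%, already exceeds the 20% assumed for the whole RCT 1 population.

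Three stated figures depend on the 20%: the cohort of 1,500, the yield of just over 300 for RCT 1, and the remainder of 900 outside the trials. If the 20% is wrong, the expected class sizes are wrong, and the calculation is tied to the trial that fills faster.

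The class shares also matter for the study's main aim. Strategies I to IV in the economic analysis are policies for a whole IVF population, so their average cost and effect depend on how many women fall in each AFC class.

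**Working it through.** **Inputs, all from the protocol article.** Cited AFC distribution: below 6, 25%; 6-9, 18%; 10-15, 33%; above 15, 24%. Assumed RCT 1 share: 20%. Entry criteria: RCT 1 AFC below 11, RCT 2 AFC above 15. Target: 300 per trial. Cohort: 1,500. Expected gains: RCT 1, 25% to 40% (15 points); RCT 2, 35% to 42% (7 points).

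**Reproducing the plan's figures.**
- Cohort: 300 / 0.20 = 1,500. Agrees.
- Remainder: 1,500 − 300 − 300 = 900. Agrees.
- Power (two-sided 0.05, pooled-variance test of two proportions, 1:1 allocation assumed): RCT 1 at 300, 79.5%; both trials together at 600, 30% against 41%, 80.5%; RCT 2 at 300, 23.7%. These match the stated 80%, 80% and 24%.

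The division is correct; the problem is the input.

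**Eligible share on the cited data.** The bands do not coincide with the trial's cut-offs, but they give bounds.
- RCT 1 (below 11): at least 25% + 18% = 43%, because AFC 10 is also eligible but sits in the 10-15 band.
- If AFC 10 holds one sixth of that band (an assumption of even spread): 43% + 33%/6 = 48.5%.
- RCT 2 (above 15): 24%, an exact match of bands.
- Normal responders (11-15): at most 33%; under even spread, 27.5%.

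**Expected composition of 1,500 women.**

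| Class | Plan | Bound from cited data | Even spread |
|---|---|---|---|
| RCT 1, AFC <11 | 300 | at least 0.43 × 1,500 = 645 | about 728 |
| RCT 2, AFC >15 | 300 | 0.24 × 1,500 = 360 | 360 |
| AFC 11-15 | not stated | at most 0.33 × 1,500 = 495 | about 413 |
| Outside the two trials | 900 | | |

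If everyone outside AFC 11-15 is randomised, the 900 must all have AFC 11-15. That is 900/1,500 = 60% of women, where the cited data allow at most 33%.

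**Screening needed for 300 in each trial.**
- RCT 1: at most 300 / 0.43 = 698.
- RCT 2: 300 / 0.24 = 1,250.

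RCT 2 is limiting, and both numbers lie below 1,500.

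**Conditional effect on the economic model.** This applies only if the enrolled proportions (60/20/20) were used as population weights. Population gain = sum of class share × expected gain in that class.
- Strategy IV (adjustment in predicted poor responders only): 0.20 × 15 = 3.0 points, against at least 0.43 × 15 = 6.45, about 6.5.
- Strategy II (adjustment in both groups): 0.20 × 15 + 0.20 × 7 = 4.4 points, against at least 0.43 × 15 + 0.24 × 7 = 8.13, about 8.1.

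**The case against.** The best defence is that the 20% is introduced as an assumption and does no harm. The cited meta-analysis may differ from the trial's population and its bands do not match, so 43% is not necessarily the trial's prevalence. This stands in part: the authors may depart from those data, but they should say why. The band mismatch does not rescue 20%, because it makes 43% a lower bound on the cited data.

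The 20% could also be taken as a consent or participation rate. The text does not allow that. It describes a share with low or low-normal reserve who are for that reason eligible, and the recruitment section describes consent before classification by AFC.

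Three stronger conclusions are tempting, and the document does not support them.

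- A reader might infer that the economic analysis is biased by 60/20/20 weights. The article gives sample sizes and says the data will be integrated; it states no weights. The gains of 3.0 and 4.4 points show what would follow from one possible choice.
- A reader might infer that the plan promises 900 normal responders. It does not. The 900 are labelled as the cohort study, and the AFC 11-15 reading comes from combining this with the randomisation rule. If each trial closes at 300, the 900 could include unrandomised women with low or high counts. That would fit the stated trial sizes but conflict with the rule that only predicted normal responders are left out.
- A reader might infer that recruitment or power is in danger. Neither is: 1,500 covers both trials. Were RCT 1 left open, 645 women would raise its power to about 98%. That case and closure at 300 are alternatives and cannot both be counted as consequences.

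**Conclusion.** The point holds as an unexplained planning input that contradicts the plan's own data. The assumed 20% is less than half of the 43% minimum implied by the preceding sentence, and the 900/300/300 composition cannot be reconciled with those data and the randomisation rule together. On the cited distribution, RCT 2 determines how many women must be screened, although the calculation is built on RCT 1.

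The result assumes that the meta-analysis distribution applies to the women screened here, which is the use the article itself appears to make of it. The lower bound of 43% needs no assumption about spread within bands; the 48.5% figure does.

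The matter should be fixed, but it does not threaten the trial: the cohort is large enough, the stated power figures reproduce, and any distortion of the economic results depends on a weighting choice that the article leaves open.

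**What to change.** 1. In Sample size calculation, replace the 20% with the prevalence from the cited data (at least 43% for RCT 1, 24% for RCT 2), or state why the trial population is expected to differ.
2. Restate the expected numbers per AFC class among 1,500 women, and say that RCT 2 sets the screening number.
3. Reconcile Study design, Sample size calculation, Recruitment and Economic analysis: say whether RCT 1 closes at 300, what happens to eligible women screened after that, and which women make up the 900.
4. In Economic analysis, add one sentence: class-specific results are weighted by the AFC distribution observed in all women screened, including any screened after a trial has closed, and not by enrolled numbers.

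The cost is a few restated figures and sentences. AFC is already measured in every woman screened, so no extra patients or measurements are needed.

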### Recruitment, consent and randomisation

Eligible women with an indication for a first IVF or ICSI treatment cycle or a first IVF or ICSI treatment cycle after birth of a child will receive oral and written information from their attending physician. The investigator will explain the study fully and in sufficient detail to allow the women to make an informed decision whether to participate or not. If a woman is willing to participate, written informed consent will be obtained. Based on AFC classification women will be entered into one of the four AFC classes (see Figure 1). Participants, excluding the predicted normal responders, will be randomly allocated to a standard or individualised FSH regime. All predicted normal responders will receive the standard dosage. Randomisation will be performed centrally by a web-based randomisation program and will be stratified by centre.

**Figure 1 F1:**
[figure not shown]
Study procedure.

### Study population

All subfertile women indicated for a first IVF or ICSI cycle, who are aged < 44 years, have a regular menstrual cycle and no major uterine or ovarian abnormalities at TVS are considered to be eligible for participation. Women with polycystic ovary syndrome (PCOS) and (uncorrected) endocrine or metabolic abnormalities, as well as women undergoing IVF after oocyte donation, will not be included.

### Study procedures

The AFC will be measured to assess ovarian reserve capacity. The AFC will be performed in the early follicular phase (cycle day 1–3) of the stimulation cycle by using a standard TVS based measurement and count of all ovarian follicles sized 2–10 mm in both ovaries, performed by experienced physicians trained in applying this ultrasound test. On the same day serum will be obtained for post hoc analysis of endocrine ovarian reserve tests. Based on the result of the AFC women will either receive a standard or elevated FSH dosage (RCT 1) or a standard or reduced FSH dosage (RCT 2). All predicted normal responders will receive the standard dose regime. Recombinant or urinary FSH will be used for ovarian stimulation. Stimulation with the assigned FSH dose will be initiated on cycle day 2 or 3. Dose adjustments in the course of the stimulation cycle are not allowed. A gonadotrophin-releasing hormone (GnRH) agonist (long or flare-up protocol) or antagonist co-treatment protocol will be used for luteinizing hormone (LH) peak suppression. The participating hospitals will apply only one of the methods of LH suppression for all participants included in the study (GnRH analogue stratification). Final oocyte maturation will be achieved by administration of human chorionic gonadotrophin (hCG) when three or more follicles of 17 mm are present. Oocyte retrieval will be carried out 34–36 hours after hCG administration. Embryo transfer will be performed 3–5 days after ovum pick- up. Luteal phase supplementation will consist of 600 mg micronized progesterone in three separate dosages starting one day after oocyte retrieval and continued until 18 days after ovum pick-up. All participants will undergo a maximum of three IVF or ICSI cycles during a treatment period of maximally 18 months.

#### Experimental group

All women in the experimental group will receive an individualised FSH dose based on their AFC. If women in RCT 1 are randomised for dose adjustment they will use 450 IU FSH/day if the AFC is below 8 and 225 IU FSH/day if the AFC is 8-10. Women in RCT 2 will receive 100 IU FSH/day if they are randomised for dose adjustment. Participants will be subjected to the assigned dosage in the subsequent cycles. In RCT 1, dose adjustments are not allowed in a subsequent cycle. For women in RCT 2, dose adjustment in the second or third cycle is allowed, and can consist of a step of 25 IU FSH/day, if there is a poor response or hyperresponse (poor response is defined as the retrieval of less than five oocytes or the cancellation of a stimulation cycle because less than two follicles above 12 mm in diameter are observed on ultrasound; hyperresponse is defined as the retrieval of more than 15 oocytes or cancellation of a stimulation cycle because more than 20 follicles over 12 mm in diameter are growing and estradiol levels exceed 11.700 pmol/L (= 3187,08 ng/L) or if more than 30 follicles over 12 mm are growing).

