#### Control group

All women in the control group will receive a standard FSH dose of 150 IU/day, independent of the AFC classification. They will be subjected to the assigned dosage in the subsequent cycles. However, based on the response in preceding cycles, a dose adjustment in the second and third cycle is allowed, but cannot exceed a step of 50 IU FSH/day, if there has been a poor response or hyperresponse (as defined above).

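### RCT 1 pools two AFC classes on two different experimental doses and carries them into one economic strategy; the trial tests the combined dosing rule, but no class-level estimate or strategy is listed

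*Protocol article*

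**What the plan says.** The Study design section of the Protocol article defines the two lower classes separately: "AFC less than 8 (predicted poor responders), AFC 8-10 (predicted low-normal responders". It then combines them: "RCT 1 will contain 300 women with an AFC below 11". The Experimental group section assigns each class its own dose: "they will use 450 IU FSH/day if the AFC is below 8 and 225 IU FSH/day if the AFC is 8-10". The Control group section has one comparator: "All women in the control group will receive a standard FSH dose of 150 IU/day, independent of the AFC classification".

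The Sample size calculation assumes a single effect for the whole of RCT 1, "an increase in pregnancy rate over three IVF or ICSI cycles of 15% (from 25% to 40%) in the predicted poor responders (RCT 1", and concludes "we need to include 300 couples in RCT 1 (alpha-error of 0.05 and a power of 80%, two-sided test". On allocation, the article states: "Randomisation will be performed centrally by a web-based randomisation program and will be stratified by centre". The Statistical analysis section compares the arms of each RCT by chi-square tests on crude rates and by life tables. Logistic and Cox regression are reserved for predictive factors; female age and duration of subfertility are the examples given, and AFC class is not named. The Economic analysis lists one low-AFC strategy, "IV. ORT followed by IVF or ICSI and dose adjustment in women with predicted poor response only", and one strategy combining it with dose reduction in predicted hyperresponders. Neither separates the two RCT 1 doses.

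**The concern.** The aim is cost-effectiveness of dosing by ovarian reserve, and the Discussion describes hormonal stimulation as the most expensive part of treatment. Each AFC class is its own dosing decision with its own drug cost. The pooled RCT 1 result weights the two classes by however many women happen to fall in each.

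A favourable pooled ratio could rest on one class while the other adds cost without gain. An unfavourable one could conceal a class in which the dose step pays for itself. As listed, the strategies offer no route to detect either.

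The labels add to this. In Study design, predicted poor responders means AFC below 8. In the Sample size calculation, the same words cover all of RCT 1.

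**Working it through.** **Inputs.** From the article: 300 women in RCT 1; 25% versus 40%; two-sided alpha 0.05; power 80%; doses 450, 225 and 150 IU/day. Assumed: 1:1 allocation (150 per arm), the same 25% and 40% in each class, no dropout.

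**1. The plan's own figure.** With the pooled-variance formula for two proportions, mean rate 0.325 and no continuity correction:

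n per arm = [1.96·√(2·0.325·0.675) + 0.842·√(0.25·0.75 + 0.40·0.60)]² / 0.15² = 152, or 304 in total.

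Power at 150 per arm is 79.5%. The stated 300 therefore reproduces, for the pooled contrast.

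**2. Class mix.** The article does not give it, because its AFC distribution (25% below 6, 18% at 6-9, 33% at 10-15) uses other cut-points. Assuming an even spread within bands:
- AFC below 8: 25 + 18·(2/4) = 34
- AFC 8-10: 18·(2/4) + 33·(1/6) = 14.5
- Share below 8: 34/48.5, about 70%

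A range is used below.

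**3. Power within each class, 25% versus 40%.**

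| Share with AFC <8 | Women per arm (<8 / 8-10) | Power (<8 / 8-10) |
|---|---|---|
| 30% | 45 / 105 | 33% / 64% |
| 50% | 75 / 75 | 50% / 50% |
| 70% | 105 / 45 | 64% / 33% |
| 80% | 120 / 30 | 70% / 23% |

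For 80% power in each class separately, 304 women per class are needed, 608 in total.

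**4. Pooled power if only one class gains 15 points.**
- 50:50 mix: pooled gain 0.5·15 = 7.5 points, power 30%.
- 70:30 mix, only AFC <8 gains: 0.7·15 = 10.5 points, power 51%.
- 70:30 mix, only AFC 8-10 gains: 0.3·15 = 4.5 points, power 14%.

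**5. Interaction, 15 versus 0 points, even mix.** Variance = (0.1875 + 0.24)/75 + (2·0.1875)/75 = 0.0107. Then 0.15/√0.0107 = 1.45, and power = Φ(1.45 − 1.96), about 31%. With 70:30 and the gain in AFC <8, it is about 27%.

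**6. Extra starting FSH.** 450 − 150 = 300 IU/day and 225 − 150 = 75 IU/day, a ratio of 4. With share s below 8, that class carries 300s/(300s + 75(1 − s)) of the extra daily dose: 80% at s = 0.5 and 90% at s = 0.7.

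**7. What the pooled ratio conceals.** Take extra starting IU/day per additional live birth as a rough stand-in for the drug component of the ICER, with an even mix. The mean extra dose is (300 + 75)/2 = 187.5 IU/day.
- Both classes gain 15 points: pooled 187.5/0.15 = 1,250; by class 300/0.15 = 2,000 and 75/0.15 = 500.
- Only one class gains: pooled 187.5/0.075 = 2,500, whichever class it is. By class, the gaining class is at 2,000 (AFC <8) or 500 (AFC 8-10), and the other has extra dose with no gain.

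The pooled ratio is identical in the two one-class cases.

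**The case against.** The intervention is the AFC-to-dose rule, and testing a rule as a whole is a legitimate design that answers the declared question. That stands. Covariate adjustment and subgroup estimates are often left to an analysis plan, which is not shown, and the article promises data for all arms. That stands in part: the crude test, the pooled sizing and the strategy list are stated here and can be judged here.

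A reader might infer three stronger points, none of which the article supports:

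- **That the trial cannot say anything about either dose.** AFC is known before allocation and both classes are randomised against 150 IU/day, so within-class comparisons are unbiased. They are imprecise, not impossible.
- **That stratifying by centre alone makes RCT 1 invalid.** Randomisation balances class in expectation. With an even mix, the chance difference between arms in the share below 8 has a 95% range of 1.96·√(2·0.25/150), about ±11 points (ignoring centre strata). If prognosis differed by an assumed 10 or 20 points between classes, an 11-point imbalance would move the effect by 1.1 or 2.2 points, against a design effect of 15. The cost is precision.
- **That Strategy IV's population is undetermined.** The abstract gives 225-450 IU/day as the individualised regime for predicted poor response, and the Sample size calculation admits low and low-normal reserve to the poor-responder trial. Together these point to AFC below 11. The label is loose, but its meaning can be recovered.

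The 300 and 75 IU/day are also starting-dose differences only. The Control group section allows steps of up to 50 IU/day in cycles 2 and 3, while RCT 1 experimental doses are fixed, so the three-cycle contrast may differ.

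**Conclusion.** The point holds as one about estimation and reporting. RCT 1 is sized for the pooled contrast and, in this article, planned only for it. The pool answers the question about the rule, but a single ICER averages two dose steps with a fourfold difference in extra starting FSH. Across assumed shares of 30% to 80% with AFC below 8, class-level power for the planned effect runs from 23% to 70%, so class results can inform the decision model but cannot settle either step.

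This rests on 1:1 allocation, equal rates in both classes, no dropout and an assumed class mix. It implies no view on which dose is appropriate.

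**What to change.** 1. Replace the crude RCT 1 comparison with one adjusted for AFC class (<8, 8-10), which is recorded before randomisation.
2. Report the treatment effect and cost difference in each class with confidence intervals, and a treatment-by-class interaction. Label these secondary and state that they are underpowered.
3. In the decision model, split Strategy IV into AFC <8 only, AFC 8-10 only, and both, carrying the class-level uncertainty through.
4. State that predicted poor response in the Sample size calculation and Economic analysis means AFC below 11, and reconcile this with the class names in Study design.

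Adding AFC class to the randomisation is optional. Two classes in 25 centres make 50 strata, about 300/50 = 6 women each, and inclusion began in May 2011, so the gain in balance may be small.

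The cost is a few more model runs on data already collected, and class-level estimates with wide intervals. No extra participants and no change of dose are needed.
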